### Planned Statistical Analyses

#### Aim 1: Analyses

The primary end point of specific aim 1 is the change in acute distress as measured by the K-6 distress scale over 1 month (immediately post intervention). To test whether eSCCIP/eSCCIP-SP is more efficacious in decreasing acute distress relative to the education control (hypothesis 1), an ANCOVA model will be estimated, which has repeatedly been shown to provide optimal estimate precision, power, and CI coverage among pretest-posttest analysis alternatives in RCTs [51,52]. The ANCOVA model will be used to test for group differences in K-6 distress scores, controlling for preintervention distress scores. Covariates will be incorporated if baseline differences are identified across site-specific, program delivery, and demographic variables. As participants may be nested within providers at each site, we will explore the need for specifying a mixed-effects model, contingent upon the size of the provider effect (eg, design effect, impact on model standard errors) and the number of providers available in the data set. With regard to families with 2 participating parents and caregivers of children with cancer, methodological research has shown poor model performance of mixed-effects dyadic models if the proportion of singletons (dyads with only 1 member) is high, as is expected for this study; therefore, primary analyses will be conducted only on primary participating caregivers [53]. We do not expect treatment effects to differ by dyad status and will test this assumption with data obtained from nonprimary participating parents analyzed in exploratory analyses. Model assumptions will be checked and alternative robust will be methods used, for instance, robust SEs, bootstrapping, or generalized linear models, if applicable [54,55]. Secondary end points (eg, PTSS and anxiety) in specific aim 1 will be analyzed in the same manner. All tests will be 2-tailed at a .05 level of significance; the Benjamini-Hochberg method will be used to adjust for multiple testing [56].

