### Study Design

This study is a multisite RCT that will enroll participants at 3 geographically diverse pediatric hospitals, which are subsequently anonymized as sites A, B, and C. Participants will be randomized to one of two treatment conditions: (1) eSCCIP/eSCCIP-SP (depending on primary language or preference) or (2) education control.

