### Randomization

Randomization will be conducted at the family level according to a 1:1 ratio between groups, in permuted blocks of 6, stratified by site and language preference. The study data analyst at site A will use an Excel (Microsoft Corp) spreadsheet with a randomization scheme created by the study biostatistician to randomize families. This spreadsheet will be inaccessible to any members of the study team aside from the data analyst. It is not possible for study telehealth guides to be blinded to the intervention condition because of the in-person contact required for eSCCIP/eSCCIP-SP; however, study investigators and research coordinators (RCs) not involved in intervention delivery will not have access to random assignment information. After randomization, participants will be instructed on the procedures within their assigned group. All outcome measures will be completed directly on the web by study participants, further reducing the risk of bias.

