### Sample Size

Based on the power analyses discussed below, 350 parents and caregivers of children with cancer will be recruited to account for a conservative 25% attrition rate. Of note, although multiple caregivers from each family are eligible to participate, the target sample size of 350 parents and caregivers of children with cancer refers specifically to 350 primary participating caregivers from unique families. Data from nonprimary participating parents will be used only for exploratory analyses. Based on the results from pilot studies, we expect approximately 20% of the 350 families recruited to include a second participating parents and caregivers of children with cancer. Recruitment, retention, and engagement strategies have been an explicit focus of previous eSCCIP research, and strategies generated from this research and the literature inform the recruitment plan [35,36]. Recruitment targets are feasible based on the number of children with cancer treated annually at sites A, B, and C (1000 per year across sites), as well as the number of English-speaking and Spanish-speaking parents and caregivers of children with cancer at each site. We expect 40%-50% of the sample to be Spanish-speaking parents and caregivers of children with cancer. Previous eSCCIP studies have had high recruitment rates (64%-70%) [24,36] as well as retention rates of over 70% in eSCCIP pilot work. Estimating 25% study attrition is an appropriately conservative approach; however, recruitment targets will be evaluated frequently and adjusted accordingly if attrition is higher than expected, given previous work.

To specifically address aim 3, parents and caregivers of children with cancer will be identified from each study site using purposive sampling across demographic groups. We will initially target 10 participants from each site (n=30), comprising 6 parents and caregivers of children with cancer (3 English-speaking and 3 Spanish-speaking), 2 psychosocial providers, and 2 oncology providers, but final recruitment will be dependent upon data saturation. We will complete interviews until no new ideas are shared, consistent with best practices for reaching saturation in qualitative research [37].

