### Data Quality

Data quality will be monitored throughout intervention implementation and data collection. The research team will routinely generate data quality reports (via built-in functionality) and meet biweekly to review the reports, discuss any identified issues (eg, missing data), and outline remedial actions. For the education control website, data from CopingSpace.org will be migrated to the same server that will host eSCCIP/eSCCIP-SP for ease of tracking and standardization. Once data collection is complete, a rigorous data cleaning, description, and covariate screening process will be carried out prior to analysis. Data will be first inspected for erroneous, outlying, or potentially high-leverage values, and missing data patterns tabulated and visualized. Data from the 3 recruiting study sites will then be pooled for analyses in 2 different versions of the data set separating participants who provide data for at least 1 measurement visit from participants who provide data at all time points. Multiple imputations will be used to handle missing data, including determination of a primary missing data mechanism, appropriate selection of auxiliary variables (if applicable), and sensitivity analyses to check for robustness of underlying assumptions (eg, MNAR selection models, pattern mixture models) [50]. Efficacy analyses will be carried out for both sets, thus providing a complete picture of whether and how missing data impact analysis results.

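### The primary ANCOVA should fix site and language, the randomization strata, as covariates; the baseline-imbalance trigger will almost never select them and leaves the primary model open until after data collection

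*Protocol article*

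**What the plan says.** Protocol article, Aim 1: Analyses, sets out the primary model: "The ANCOVA model will be used to test for group differences in K-6 distress scores, controlling for preintervention distress scores". Baseline K-6 is the only covariate fixed in advance. The next sentence governs every other one: "Covariates will be incorporated if baseline differences are identified across site-specific, program delivery, and demographic variables". Secondary end points follow the same approach, so the rule carries over to them.

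Randomization states that families are allocated "according to a 1:1 ratio between groups, in permuted blocks of 6, stratified by site and language preference". Study Design gives "3 geographically diverse pediatric hospitals", and Sample Size says "We expect 40%-50% of the sample to be Spanish-speaking".

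Data Quality places covariate screening late: "Once data collection is complete, a rigorous data cleaning, description, and covariate screening process will be carried out prior to analysis".

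Language appears again in Aim 2: Analyses, but as a moderator. Limitations adds that use of other psychosocial services during the study may be controlled for if this seems indicated.

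**The concern.** Three features of the rule are unsatisfactory.

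- **Strata.** Stratified blocking forces site and language to be nearly equal across arms. A rule that adds a covariate only when the arms differ therefore passes over the factors on which the trial was randomized. The usual standard error then ignores precision that the design has already provided.
- **Selection.** In a properly randomized trial, a baseline difference between arms is chance. Imbalance does not show that a variable predicts K-6, so the rule can add irrelevant covariates and omit useful ones. The choice is made once outcomes exist.
- **Program delivery.** The candidate list includes this class without defining it. In this article, delivery mostly concerns cores, telehealth sessions and guides, which follow randomization, and Education Control says the control arm has no videos or telehealth sessions. If such a variable entered the primary model, the estimate would be biased.

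At stake are some precision and the prespecification of the primary model. The validity of the randomized comparison is at stake only if a variable from after randomization were admitted.

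**Working it through.** **1. The plan's own figure.** Inputs from Power Analyses and Sample Size Consideration: difference 0.3 SD, pre-post correlation 0.5, two-sided .05, 80% power, 25% attrition. Residual SD = √(1 − 0.5²) = 0.866.

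n per arm = 2 × (1.960 + 0.842)² × 0.75 / 0.3² = 131, so 262 in total; 262 / 0.75 = 349.3, rounded up to 350. Power at 131 per arm is 0.801 (0.798 with the noncentral t on 259 df). The planned 350 reproduces, with no slack.

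**2. Can the trigger select the strata?** Three sites × two languages = 6 strata. In a block of 6 the arms can differ by at most 3 per stratum:

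- per site: 2 strata × 3 = 6
- per language: 3 strata × 3 = 9

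Take 350 families, equal sites (assumed) and 45% Spanish-speaking (the middle of the stated range). For the worst site case, two sites are each split 61.5 : 55.5 in opposite directions: χ² = 4 × 3² / 58.5 = 0.615 on 2 df, p = 0.74. For the worst language case: χ² = 2 × 4.5² / 78.75 + 2 × 4.5² / 96.25 = 0.935 on 1 df, p = 0.33. Neither can reach .05 at randomization.

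In 5000 simulated trials the smallest p at randomization was 0.58. After 25% nondifferential attrition, site was flagged in 0% and language in 0.02%; a separate simulation gave at most 0.03%.

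**3. What omission costs.** Assumption: site and language explain a share R² of the K-6 variance left after baseline adjustment. Results from 5000 simulated trials per row, with 25% attrition (Monte Carlo error on a type I error near .05 is about √(0.05 × 0.95 / 5000) = 0.003):

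| R² | Type I error, strata omitted | Type I error, strata included | Power, omitted | Power, included |
|---|---|---|---|---|
| 0% | 0.053 | 0.053 | 0.80 | 0.80 |
| 5% | 0.045 | 0.050 | 0.805 | 0.817 |
| 10% | 0.040 | 0.049 | 0.805 | 0.836 |
| 20% | 0.036 | 0.050 | 0.810 | 0.874 |

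The analytic check for the adjusted model, with residual SD √(0.75 × (1 − R²)), gives power 0.820, 0.840 and 0.880 for 5%, 10% and 20%. The simulated loss is 0.817 − 0.805 = 0.012 up to 0.874 − 0.810 = 0.064, that is, about 1 to 6 points. With exact balance, the type I error of the unadjusted test is 2 × [1 − Φ(1.96 / √(1 − R²))] = 0.044, 0.039 and 0.028, in line with the simulation.

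**4. How often chance imbalance changes the model.** For k independent baseline variables tested at .05, the chance of at least one flag is 1 − 0.95^k: 0.23 for k = 5, 0.40 for k = 10, 0.54 for k = 15. The article gives neither k nor a threshold; these are illustrations.

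**5. Does that selection inflate error?** With 262 analysed, 10 independent baseline covariates screened at .05 and added when flagged (8000 runs), type I error was 0.051, 0.047 and 0.045 when the covariates explained 0%, 10% and 30% of residual variance. The mean estimate under a true 0.3 was 0.300-0.303. Taking the smaller of the adjusted and unadjusted p-values gave 0.054-0.059.

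**6. If a variable from after randomization were admitted.** Assume it differs between arms by 0.5-1.0 SD and has residual correlation 0.1-0.3 with the outcome (4000 runs, 262 analysed). With no true effect, bias is 0.04-0.26 SD and type I error 0.07-0.62. A true 0.3 SD effect shrinks to between 0.26 and 0.04 SD.

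**The case against.** The strongest case for the plan has four parts.

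- *Omitting the strata is safe.* The estimate stays unbiased, the test is conservative, and 350 gives 80% power without stratum adjustment. This stands. The point is about efficiency, and the size of the gain rests on an assumed R².
- *The trigger does not corrupt the test.* A reader might infer that choosing covariates by imbalance leaves the error rate uncontrolled. The document does not support that, and step 5 shows type I error at or below about .05 for the rule applied mechanically. The 40% figure is how often a covariate is added, not how often a false positive occurs. What remains is that the model is undetermined until after data collection and the selection criterion is the wrong one.
- *Program delivery need not mean anything after randomization.* The sentence requires a baseline difference, which a variable that does not yet exist cannot show. The term could refer to language version or access route, and Aim 2: Analyses treats engagement descriptively. A reader might infer that the plan commits to adjusting for delivery in the primary model; it does not say so. The wording is open, and the allowance in Limitations for controlling for services used during the study shows why it should be closed.
- *Site and language are not ignored.* Site-specific variables are candidates, a provider-level mixed model is considered, and language is a planned moderator. This is true, but none of it commits the primary model to either factor.

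A threshold and variable list may well be left to the analysis plan. The trigger itself is stated here, so it is not a missing detail.

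**Conclusion.** The point holds as a should-fix, free improvement. The imbalance trigger almost never selects site or language. To say that it cannot select them would go too far: screening comes after data collection, and differential dropout could unbalance either factor in the analysed set. The percentages in step 2 assume nondifferential attrition and a .05 threshold.

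The consequence is an oversized standard error, not bias or false positives. Its size depends wholly on the assumed 5-20% of residual variance; at 0% there is nothing to gain. Prespecification is weakened because the primary model depends on chance imbalance. The bias figures in step 6 apply only if the undefined delivery class is taken to include variables from after randomization, and they rest on assumed shifts and correlations.

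**What to change.** Replace the covariate sentence in Aim 1: Analyses with:

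> The primary ANCOVA will include treatment, baseline K-6, site and language for all participants regardless of observed balance; any further covariates will be pre-randomization variables named in advance for prognostic value.

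Keep program delivery and service-use variables for aim 2 or exploratory analyses, and align the service-use remark in Limitations. The screening in Data Quality can stay as data description but should not choose primary-model covariates.

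Cost: a wording change and about 3 degrees of freedom (2 for site, 1 for language). The sample size of 350 does not change.

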### Power Analyses and Sample Size Consideration

The primary end point of the study is to compare posttest differences in distress post intervention between intervention and education control groups. In a recent pilot study of 14 participants, we detected a mean change of 1.71 (SD 2.09) in distress on the distress thermometer at 1 month in the English version of the questionnaires. In standardized form, the effect size is 0.82. We do not have an estimate of the impact of the education control group on our primary end point; however, we expect no more than a modest to medium effect (0.2 to 0.5). Therefore, we are planning a sample size to detect a difference in effects between the groups of at least 0.3. Power analyses based on the analysis of covariance (ANCOVA) model and assuming a correlation of at least 0.5 between pretest and posttest scores suggest that a sample size of 350 individual parents and caregivers of children with cancer (175 in each group) can detect a difference of ≥0.3 in standardized mean distress reduction between intervention and education group conditions with a power of at least 80% at the level of significance of .05 and assuming an attrition rate of 25%. Therefore, a sample size of 350 is planned for this study.

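### The multiplicity sentence does not exempt the single primary K-6 test, while the sample size assumes that test is made at an unadjusted .05

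*Protocol article*

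**What the plan says.** The protocol article has one primary hypothesis: less acute distress after the intervention, measured by the K-6 and tested by ANCOVA. The secondary hypothesis in Study Objectives covers four constructs: posttraumatic stress symptoms, anxiety, coping self-efficacy and positive cognitive coping.

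Aim 1: Analyses sets out the primary model, says the secondary endpoints get the same analysis, and ends with the only multiplicity rule for this aim: "All tests will be 2-tailed at a .05 level of significance; the Benjamini-Hochberg method will be used to adjust for multiple testing". It does not list the tests in the family or say where the primary test stands. Aim 2: Analyses names Benjamini-Hochberg again, for the moderator interaction tests.

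Power Analyses and Sample Size Consideration plans 350 caregivers, 175 per arm, to show a standardized difference of 0.3 "with a power of at least 80% at the level of significance of .05". The calculation allows for 25% attrition, "assuming a correlation of at least 0.5 between pretest and posttest scores". It mentions no multiplicity adjustment.

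**The concern.** The rule follows directly on the primary and secondary Aim 1 tests and opens with all tests as its subject. With no exemption stated, the most natural reading puts K-6 in the family. The level at which K-6 is judged would then depend on how the other outcomes turn out.

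Take a family of five and a K-6 p-value of .03. If no secondary reaches .05, K-6 ranks first, is compared with .01, and fails. If two secondaries are also at or below .03, the third-ranked threshold is 3 × .05/5 = .03, and K-6 passes. The same primary result gets opposite verdicts.

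Two things are at stake. The trial could miss its primary endpoint because of secondary outcomes, and the power quoted would not be the power of the test carried out. A single prespecified primary test needs no multiplicity adjustment of its own, so nothing is gained in return.

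**Working it through.** **Inputs from the article.** Standardized difference 0.3; pretest-posttest correlation 0.5; two-sided alpha .05; 175 per arm; 25% attrition; 1:1 allocation; five constructs (K-6 plus the four in the secondary hypothesis).

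**Assumptions.** One test per construct, so m = 5. The article gives no secondary effect sizes and no correlations between endpoints. Secondary effects were varied from none upwards, and the correlation between test statistics was set at 0.3 and 0.5.

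**1. The stated figure.** The ANCOVA residual SD is √(1 − 0.5²) = 0.866.

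- n per arm = 2 × (1.960 + 0.842)² × 0.75 / 0.3² = 130.8, so 131.
- 131 / 0.75 = 174.7, so 175 per arm and 350 in total.
- Noncentrality = 0.3 / (0.866 × √(2/131)) = 2.80.
- Power at two-sided .05 = Φ(2.80 − 1.96) = 80.1% (79.8% with the noncentral t).

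The stated sample size reproduces for one unadjusted test, with nothing to spare.

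**2. Thresholds if K-6 is one of five.** Benjamini-Hochberg compares the ordered p-values with .05 × k/5, that is .01, .02, .03, .04 and .05. The largest k that meets its threshold sets the cut-off for all five. K-6 therefore faces .01 when only one test can be rejected and .05 when all five are. At .01 its power is Φ(2.80 − 2.576) = 59.0%.

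**3. K-6 power under the step-up rule.** Simulation with at least 200,000 replicates per scenario, K-6 noncentrality 2.80:

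| Secondary effects (all four) | K-6 power, m = 5 |
|---|---|
| None | about 60% |
| Half the planned effect | about 62% to 64% |
| Equal to 0.3 | 75% to 76% |
| Clearly larger (noncentrality 4) | about 80% |
| K-6 tested alone at .05 | 80% |

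If two of the four secondaries have the 0.3 effect and two are null, K-6 power is about 70%.

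**4. Cost of keeping K-6 in the family.** At the strictest threshold (.01), 80% power needs 195 evaluable per arm: 2 × 195 / 0.75 = 520 caregivers instead of 350.

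**5. Effect on the secondaries of taking K-6 out.** With one true secondary (0.3 effect) and three null, power for the true one falls from about 65.6% in a family of five to about 62.6% in a family of four (correlation 0.3). With all four at half effect, power for each falls from about 20.6% to 19.0%.

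**The case against.** The strongest reply is that the sentence has two clauses. All tests is the subject of the first, "All tests will be 2-tailed at a .05 level of significance"; the second, "the Benjamini-Hochberg method will be used to adjust for multiple testing", does not say which tests it covers. One primary hypothesis need not count as multiple testing, and the power section plans that test at a plain .05. On this reading Benjamini-Hochberg covers the secondaries only, the two sections agree, and the 80% stands. The reading is possible, and a reader should not infer that the article expressly puts K-6 in the family. But it needs an exemption that the text does not give.

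A second reply is that the full protocol or SAP, not shown, may define the family. That is a fair answer to a complaint about missing detail. It does not remove the point that the article states a rule and a power claim which, on the more natural reading, do not agree.

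Third, the loss is not fixed. The 60% figure needs every secondary to be null while K-6 has its full effect, whereas the trial hypothesizes benefit on all of them. At equal effects the loss is 4 to 5 points, and with larger secondary effects it almost vanishes. This stands and limits the size of the finding.

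A reader might also count each coping self-efficacy domain and each of the nine cognitive coping strategies as a test, which gives a larger family and a bigger loss. The article describes these as features of the instruments, not as a list of endpoints, so those figures are not supported.

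Finally, Benjamini-Hochberg at .05 never rejects a p-value above .05. Including K-6 cannot inflate its type I error; the cost is power and clarity.

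**Conclusion.** The point holds as an unresolved mismatch between the multiplicity rule and the sample size statement. It does not show that the stated power is wrong. If K-6 is in the family, as the wording suggests, its power is about 60% to 76% for secondary effects between none and 0.3, against the stated minimum of 80%, and approaches 80% only when secondary effects are clearly larger. If K-6 is outside the family, the 80% is correct at 350.

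The figures rest on five tests, one per named construct, and on assumed secondary effects and correlations of 0.3 to 0.5. The mismatch should be settled before analysis, because with the family left open K-6 could be judged at different levels according to how the family is later drawn.

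**What to change.** Replace the closing sentence of Aim 1: Analyses with wording such as: K-6 at T2 is tested alone, two-sided at .05, without multiplicity adjustment; Benjamini-Hochberg at .05 applies to the Aim 1 secondary endpoints, listed by name, as a separate family. The Aim 2 moderator tests already have their own statement and need no change.

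This makes the power claim true at 350 caregivers. The cost is one sentence and a possible small loss for the secondaries, at most about 3 points in the scenarios checked. The loss arises because a significant primary no longer helps to relax their thresholds. If the investigators do want K-6 inside the family, the power section should say so and give the power of that test under stated secondary effects.
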